### Baseline assessment

2.5

The baseline assessment includes a mix of self-report assessments of primary outcome variables at baseline (see Table 1) and other demographic and clinical characteristics. The baseline self-report assessments are administered by a research assistant using REDCap. Final eligibility is confirmed after conclusion of the baseline assessment. Patients who present with active psychotic or manic symptoms are further assessed using the Mini-International Neuropsychiatric Interview (MINI) (42); if symptoms are deemed to be active, untreated, and likely to interfere with study procedures, these participants are deemed ineligible and provided additional internal and external resources for treatment and other psychosocial support.

**Table 1 tab1:** Study outcomes measured at baseline, post-core follow-up, and final follow-up assessments.

Study outcomes and associated measures	Timeframes		
	Baseline (BL)	Post core follow-up (~6–12 weeks post-BL)	Final follow-up (~18–24 weeks post-BL)
Effectiveness outcomes (Primary)			
Methadone treatment retention - *Defined dichotomously as retention (yes/no) in methadone treatment* - Medical chart extraction		X	X
Methadone treatment persistence - *Calculated as the proportion retained on methadone treatment monthly (*i.e.*, at least one methadone dose for each 30 day period)* - Medical chart extraction		X	X
Implementation outcomes (Secondary)			
Intervention feasibility % patients who initiated intervention Qualitative interviews		X	
Intervention acceptability % patients enrolled who attended ≥75% core intervention sessions Qualitative interviews		X	
Intervention fidelity % of intervention components delivered as intended (20% of sessions, randomly selected)		X	
Other outcomes			
Effectiveness			
Changes in depressive symptoms			
PHQ-8	X	X	X
Changes in substance use			
Urinalysis Timeline Followback	X X	X X	

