##### Methadone treatment retention

2.12.1.1

The primary effectiveness outcome for this trial is methadone treatment retention, which is assessed over six months post baseline. Methadone treatment retention is examined through clinical records of appointment attendance and determined based on one or more methadone treatment-related visit(s) attended for each 30-day period during the six months following baseline. The primary outcome is retention assessed dichotomously (i.e., yes/no) at approximately six months post baseline. Participants who are referred to another internal treatment program or transferred to an external methadone treatment program are considered retained at six months based on clinic-verified records. To supplement the dichotomous measure of retention, we will also assess methadone treatment persistence, defined as the proportion retained on methadone treatment monthly over six months (i.e., at least one methadone dose for each 30-day period) post baseline, and days retained in treatment.

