##### Quantitative

2.15.1.1

Utilizing a conservative intent-to-treat framework, all participants randomized will be included in analyses. We will examine the baseline equivalence of the groups by comparing participants receiving *Peer Activate* and TAU on sociodemographic characteristics, including sex, age, socioeconomic variables, severity of substance use, and days in treatment. Additional preliminary analyses will be conducted, including evaluating distributional assumptions of variables of interest. We will also examine patterns of missingness across treatment groups to detect deviations from missing at random (MAR) assumptions.

Effectiveness outcomes are evaluated primarily at the six-month follow up as well as at the three-month follow up post baseline. Dichotomous outcomes (including retention defined as retained/not retained at each data point) will be examined using generalized linear mixed modeling (GLMM) which allows for the inclusion of both categorical and continuous predictors as well as correlated observations across time. Two-level, mixed-effects models will be used to examine primary hypotheses. Time points (baseline, post-core follow-up, and final follow-up assessments) are nested within participants. Results will be expressed as either odds ratios (for binary, primary outcomes) or mean differences (for continuous, secondary and exploratory outcomes).

Using standard model-building procedures, treatment condition will be entered as the primary predictor in each model. We will then add additional covariates as indicated by our preliminary analyses, including days in treatment and substance use severity. We will also examine a time by group interaction which, if significant, would indicate that differences between treatment conditions become more or less pronounced across assessment points. *Post hoc* differences between treatment condition at three-month and six-month time points will also be examined using a logit link. To model days in treatment, we will conduct survival analysis using a frailty model to predict lapse in treatment and compare survival curves between treatment conditions, including random effect for PRS. We will assess levels of skew in the days in treatment outcome variable and accommodate our approach accordingly.

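### The model named for the primary hypotheses pools the treatment effect over three assessment rows, while the six-month contrast, which is the primary outcome, is left as post hoc

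*Protocol article*

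**What the plan says.** All references are to the protocol article.

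- **Outcome (2.12.1.1 Methadone treatment retention).** "The primary outcome is retention assessed dichotomously (i.e., yes/no) at approximately six months post baseline". Retention is "determined based on one or more methadone treatment-related visit(s) attended for each 30-day period during the six months following baseline". Clinic-verified referrals and transfers count as retained at six months. Retention at three months is listed as secondary (2.12.2).
- **Schedule (Table 1, under 2.5 Baseline assessment).** Retention, "Defined dichotomously as retention (yes/no) in methadone treatment", carries two marks, which read as the two follow-ups. PHQ-8 carries three, including baseline.
- **Model (2.15.1.1 Quantitative).** Two-level mixed models serve the primary hypotheses. "Time points (baseline, post-core follow-up, and final follow-up assessments) are nested within participants", and "treatment condition will be entered as the primary predictor in each model". Covariates and a time by group interaction follow. Post hoc "differences between treatment condition at three-month and six-month time points will also be examined using a logit link". The same section says that effectiveness is evaluated primarily at six months, and that binary primary outcomes are reported as odds ratios.
- **Planning (2.14).** Control retention 0.5 at 180 days, a difference of 0.18, 100 per group, two-tailed alpha 0.05.

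**The concern.** The outcome section and the sample size section both concern a single comparison at six months. The analysis section attaches the primary hypotheses to a repeated-measures treatment term instead. At least three results could then be presented as the main one: the pooled treatment term, the interaction, and the six-month contrast. Only the last matches the declared outcome, and it has the weakest label. If the effect differs between three and six months, these results can fall on different sides of 0.05.

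Two features of the retention data make the model a poor fit as well. A baseline row is very likely constant. And because retention requires a visit in every 30-day period, retained at six months implies retained at three, which can destabilise a random-intercept logistic model.

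**Working it through.** **Inputs.** From 2.14: six-month retention 0.50 (control) and 0.50 + 0.18 = 0.68 (treated), 100 per arm. Baseline retention is taken as 1.00 in both arms, inferred from eligibility (2.2). Three-month rates are not in the document, so four assumed pairs are used.

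**The plan's own figures.** The six-month odds ratio implied by planning is (0.68/0.32)/(0.50/0.50) = 2.125. The stated 80% power does not reproduce for a two-proportion comparison. With pooled proportion 0.59, power = Φ{[0.18 − 1.96·√(2·0.59·0.41/n)]/√[(0.50·0.50 + 0.68·0.32)/n]}, which is about 74% at n = 100 and 64% at n = 80 per arm. This is a separate matter, and nothing below depends on it.

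**Step 1: what the pooled term estimates.** With treatment as the only predictor and no interaction, the marginal odds ratio compares the arms' average retention over rows. For assumed three-month rates of 0.65/0.80:

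- control: (1 + 0.65 + 0.50)/3 = 0.717, odds 2.529
- treated: (1 + 0.80 + 0.68)/3 = 0.827, odds 4.769
- odds ratio: 4.769/2.529 = 1.89

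The p values come from a marginal repeated-measures logistic model fitted to expected counts.

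| Three-month, control/treated (assumed) | Pooled OR, three rows | p | Six-month OR | p |
|---|---|---|---|---|
| 0.65/0.80 | 1.89 | 0.008 | 2.125 | 0.010 |
| 0.70/0.75 | 1.55 | 0.066 | 2.125 | 0.010 |
| 0.75/0.75 | 1.42 | 0.140 | 2.125 | 0.010 |
| 0.60/0.85 | 2.31 | 0.0005 | 2.125 | 0.010 |

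The six-month effect is the same in every line, yet the pooled result crosses 0.05.

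Removing baseline does not remove the pooling. For 0.75/0.75, the control mean is (0.75 + 0.50)/2 = 0.625 (odds 1.667) and the treated mean is (0.75 + 0.68)/2 = 0.715 (odds 2.509). The odds ratio is 1.51, still not 2.125.

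**Step 2: the baseline row.** If everyone is retained at baseline, that row cannot differ by arm. With categorical time, a time by group interaction and baseline as reference, the fit separates: standard errors were about 21,600 to 30,500.

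**Step 3: whether the mixed-model odds ratio is finite.** The random-intercept logistic likelihood was integrated numerically and profiled over the random-intercept SD, with three-month rates 0.65/0.80 and 100 per arm.

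With a categorical time term and cumulative coding, only three follow-up histories exist: yes-yes, yes-no and no-no.

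| SD | Log-likelihood | Treatment log-OR |
|---|---|---|
| 0 | −246.8 | 0.76 |
| 4 | −191.2 | 2.1 |
| 16 | −183.78 | 7.47 |
| 32 | −183.72 | 14.9 |

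The likelihood keeps rising and then flattens, while the log-OR grows in proportion to the SD (a log-OR of 7.47 is an OR of about 1,750). There is no finite maximum. Adding or dropping the baseline row does not change this.

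Under other readings the maximum is finite:

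- **Treatment only, no time term, three rows:** the log-likelihood is −306.8 at SD 1, −305.3 at SD 1.5 and −307.4 at SD 2, so it peaks near SD 1.5 with OR about 2.4.
- **Time term, point-in-time status, 6 returners per arm:** the peak lies between SD 2 and 3 (−227.5 and −227.1, against −229.6 at SD 4), with OR about 3.4 to 4.9.

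**The case against.** The strongest reply is that this is a condensed article. Time coding, model terms and handling of separation usually sit in an analysis plan that is not shown. The section also says that effectiveness is evaluated primarily at six months, and it contains a six-month contrast. A reader might infer that six months is never estimated; the text does not support that. What stands is narrower: the article itself says which model carries the primary hypotheses and which predictor is primary, and calls the six-month comparison post hoc. That is a conflict in what is written, not an omission.

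A reader might also infer that the planned odds ratio can never be finite. That needs both a time term and cumulative coding at each visit. The article gives no time main effect explicitly, although the planned interaction implies one. Its phrase about retention at each data point can be read as status at that visit. The transfer rule is worded for six months only, so a no-then-yes history is possible. Each of these can give a finite fit.

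Three further limits are fair. The nesting sentence covers all outcomes in these models, and PHQ-8 and substance use do have baseline values, so a two-row retention model is a reasonable joint reading with Table 1. All-yes baseline retention is an inference. And a conditional odds ratio above the marginal 2.13 is ordinary non-collapsibility, not evidence of bias.

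The aim of examining missingness "to detect deviations from missing at random (MAR) assumptions" is loosely worded, since observed patterns cannot show this. It is not specific to retention and does not bear on this point.

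**Conclusion.** The point holds as a mismatch between the declared primary outcome and the term given primary status in the model. Its size depends on three-month rates that the document does not give. Over the four assumed pairs, the pooled three-row odds ratio is 1.42 to 2.31 against a fixed six-month value of 2.125, with p from 0.140 to 0.0005 against 0.010. Following the plan as written could therefore change the trial's conclusion.

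The baseline row adds nothing for retention, provided that essentially everyone is in treatment at entry. The absence of a finite odds ratio is a conditional risk, confined to a model with a time term and cumulative coding. It is a further reason to avoid this model for retention, not a certain failure.

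**What to change.** 1. Name the between-arm contrast in six-month retention as the single primary test. Use logistic regression of six-month yes/no retention on arm plus pre-specified baseline covariates, in all randomized participants.
2. Report the risk difference and the marginal odds ratio, each with a 95% confidence interval. The risk difference is on the scale of the 0.18 used for planning.
3. Keep the existing rule that clinic-verified referrals and transfers count as retained.
4. State that baseline is not a retention outcome row, in line with Table 1.
5. Analyse three-month retention separately as secondary, and keep the mixed models for PHQ-8 and substance use.

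The cost is wording in the analysis section. No data collection changes, and the primary model becomes simpler. The change should be made before outcome data by arm are seen.

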### Eligibility criteria

2.2

Inclusion criteria for study eligibility are: (1) ≥18 years of age; and (2) initiating treatment in the methadone treatment program in the last three months (and having been enrolled in methadone treatment for at least two weeks) or demonstrating challenges with methadone adherence within the last three months, defined as: (a) at least one missed methadone dose in the past three months; (b) at least one missing methadone take-home bottle at the time of bottle return; (c) negative urine toxicology results for methadone in the past three months; and/or (d) transition from extended methadone take-homes to daily dosing due to concerns regarding adherence. These criteria were developed based on physician and stakeholder feedback and piloted previously (24). Exclusion criteria include: (1) pregnant at study enrollment; (2) untreated or undertreated psychosis or mania that would interfere with study participation; and/or (3) inability to provide informed consent in English.

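### Covariates enter the primary retention model according to preliminary analyses of the trial's own data, and no single model is named as primary

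*Protocol article*

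**What the plan says.** The rule is in the protocol article, section 2.15.1.1 (Quantitative). Treatment condition goes into each model first. Then: "We will then add additional covariates as indicated by our preliminary analyses, including days in treatment and substance use severity". Earlier in the same section, three preliminary analyses are described:

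- **Comparison of the arms at baseline:** "We will examine the baseline equivalence of the groups by comparing participants receiving" the intervention and usual care on sociodemographic characteristics, "including sex, age, socioeconomic variables, severity of substance use, and days in treatment".
- **Distributional checks:** "Additional preliminary analyses will be conducted, including evaluating distributional assumptions of variables of interest".
- **Missingness by arm:** "We will also examine patterns of missingness across treatment groups to detect deviations from missing at random (MAR) assumptions".

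No threshold for entry, closed covariate list or designated primary model is given. The label of one named covariate is also used for an outcome in that section: "To model days in treatment, we will conduct survival analysis using a frailty model".

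Section 2.2 (Eligibility criteria) admits patients either for "initiating treatment in the methadone treatment program in the last three months" or for "demonstrating challenges with methadone adherence within the last three months". Section 3.1 (Design considerations) reports that, in the team's preliminary work, retention was hardest in the first month after starting methadone.

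**The concern.** A covariate earns its place in a randomized comparison by predicting the outcome, and that is known or assumed before the data are seen. Under the stated rule, what enters depends on what the preliminary analyses show. Both named covariates come from the baseline-comparison list, so observed imbalance between the arms is the most natural trigger.

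Three things are at stake. First, a strong predictor that happens to be balanced may be left out, and its precision is lost. Second, the odds ratio from a logistic model changes with the covariates in it, even under perfect balance, so the quantity being estimated is not settled until the data are in. Third, an unadjusted and one or more adjusted results will exist, with nothing in the text to say which one answers the primary question.

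**Working it through.** **The plan's own figure.** Section 2.14 states 80% power for a difference of 0.18 from a control retention of 0.50, with 100 per arm, 20% attrition and two-sided alpha 0.05. With the pooled two-proportion formula, the average proportion is 0.59.

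- 100 per arm: (0.18 − 1.96 × √(2 × 0.59 × 0.41/100)) / √((0.25 + 0.2176)/100) = (0.18 − 0.1363)/0.0684 = 0.639, so power is 73.9%.
- 80 per arm: (0.18 − 0.1524)/0.0765 = 0.361, so power is 64.1%.

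The stated 80% is not reproduced. That is a separate matter: the figure does not depend on the covariate rule and neither supports nor weakens this point.

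**Cost of the covariate rule.** The article gives no covariate strengths, so this rests on a simulation.

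- From the article: 200 patients, 1:1 allocation, two-sided alpha 0.05, and a treatment odds ratio of (0.68/0.32)/(0.50/0.50) = 2.125, or 1 under the null.
- Assumed: one binary baseline predictor split 50:50 (for example recent initiation) with an odds ratio for retention of 1.5, 2.5 or 4; one continuous predictor (for example severity) with a log-odds of 0.7 per SD; all 200 evaluable; logistic regression at one time point; a predictor selected when a baseline t-test gives p < 0.05.
- 4,000 trials per scenario. The Monte Carlo standard error is √(0.05 × 0.95/4000) = 0.34 points for type I error and about √(0.67 × 0.33/4000) = 0.74 points for power.

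With two candidates, the expected chance of selecting at least one is 1 − 0.95² = 9.75%; the simulation gave 9.6–11.0%. The rule therefore leaves the model unadjusted in about nine trials out of ten.

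| Odds ratio of binary predictor | Power, no adjustment | Power, balance-selected | Power, fixed set | Fixed minus selected | Verdict differs, unadjusted vs fixed |
|---|---|---|---|---|---|
| 1.5 | 66.8% | 66.9% | 70.7% | 3.8 points | 9.9% |
| 2.5 | 63.4% | 63.0% | 67.3% | 4.3 points | 10.75% |
| 4 | 58.3% | 59.0% | 65.0% | 6.0 points | 13.8% |

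| Odds ratio of binary predictor | Type I, balance-selected | Type I, fixed set | Type I, most favourable of four sets | Average OR, unadjusted | Average OR, fixed set |
|---|---|---|---|---|---|
| 1.5 | 5.3% | 5.1% | 7.3% | 2.00 | 2.19 |
| 2.5 | 5.1% | 4.9% | 8.2% | 1.94 | 2.16 |
| 4 | 4.9% | 5.2% | 8.6% | 1.87 | 2.16 |

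The last column of the first table counts trials, under the alternative, in which significance differs between the unadjusted and the fully adjusted model. The four sets in the second table are none, each predictor alone, and both.

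**The case against.** The strongest reply is that the sentence names two covariates and can be read as a commitment to them, and that a condensed article may leave the final list to the analysis plan. The first part has some force: on that reading the fix only states the intention openly. But the wording still makes entry conditional and leaves the list open. The second part does not dispose of the point, because the article does not stay silent. It states a rule that an analysis plan following it would inherit.

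It is also fair that nothing confines selection to baseline imbalance. A reader might infer that covariates enter only through the comparison of arms. The text describes two other kinds of preliminary analysis and speaks of comparing, not testing. What stands is that all three depend on trial data.

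A reader might further infer that the two entry routes in section 2.2 split the sample into two retention-risk groups that the model ignores. The article does not support this. The routes are joined by an or, so a recent initiator with a missed dose meets both. No retention rate by route is given, and section 2.14 uses a single control rate of 0.5. If half the sample retained at 50% and half at 80%, control retention would be (0.50 + 0.80)/2 = 65%, which does not match. Pre-baseline days in treatment, already named, carries much of the same information. A chance imbalance between arms in entry route would be ordinary randomization variability, already covered by the standard error, and not bias.

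Finally, a reader might take days in treatment as the post-randomization outcome and conclude that adjustment would remove the treatment effect. The section lists it among the baseline characteristics, so this is only an ambiguous label.

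**Conclusion.** The point holds in a limited form. The stated rule makes the primary model and its odds ratio depend on trial data, and no model is designated as primary.

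Under the assumptions above, the rule performs about as well as no adjustment and forgoes about 4–6 points of power. The average odds ratio lies between 1.87 and 2.00 unadjusted and at about 2.2 adjusted. In 10–14% of simulated trials with a true effect, the choice between those two models changes the significance verdict.

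It would be tempting to say that the rule inflates the false-positive rate. The calculation does not show that: selection by balance alone gave 4.9–5.3%. The 7–9% figure arises only if the most favourable of several covariate sets were reported, and nothing in the article proposes this. It measures the room left open, not an expected error rate.

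All sizes depend on the assumed predictor strengths, the p < 0.05 entry rule and a single-time-point model in place of the planned mixed model. That the model is data-dependent follows from the wording alone.

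**What to change.** Replace the covariate sentence in section 2.15.1.1 with: 'The primary model adjusts, regardless of observed balance, for days in methadone treatment before baseline and baseline substance use severity; this adjusted model is primary and the unadjusted result is supportive.'

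Report baseline characteristics by arm descriptively, not as a model-building step. Label the covariate 'pre-baseline days in treatment' to separate it from the days-in-treatment outcome.

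Because section 3.1 reports the greatest retention difficulty in the first month after initiation, recent initiation may be added as a fixed covariate. Define it as within three months of starting, yes or no, so that a patient who meets both entry criteria is classified once.

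The cost is small. Recent initiation is ascertained for eligibility and the other two variables are already listed for the baseline comparison, so no new data are needed. The price is a few degrees of freedom and an odds ratio that is conditional rather than marginal, which the report should say. The change should be made before any outcome is examined by arm.
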